# An equivalence evaluation of a nurse-moderated group-based internet support program for new mothers versus standard care: a pragmatic preference randomised controlled trial

**DOI:** 10.1186/1471-2431-14-119

**Published:** 2014-05-06

**Keywords:** Nurse, Internet-based interventions, Early childhood, Mothers, Program evaluation

## Abstract

**Background:**

All mothers in South Australia are offered a clinic or home-visit by a Child and Family Health community nurse in the initial postnatal weeks. Subsequent support is available on request from staff in community clinics and from a telephone helpline. The aim of the present study is to compare equivalence of a single clinic-based appointment plus a nurse-moderated group-based internet intervention when infants were aged 0–6 months versus a single home-visit together with subsequent standard services (the latter support was available to mothers in both study groups).

**Methods/Design:**

The evaluation utilised a pragmatic preference randomised trial comparing the equivalence of outcomes for mothers and infants across the two study groups. Eligible mothers were those whose services were provided by nurses working in one of six community clinics in the metropolitan region of Adelaide. Mothers were excluded if they did not have internet access, required an interpreter, or their nurse clinician recommended that they not participate due to issues such as domestic violence or substance abuse. Randomisation was based on the service identification number sequentially assigned to infants when referred to the Child and Family Health Services from birthing units (this was done by administrative staff who had no involvement in recruiting mothers, delivering the intervention, or analyzing results for the study). Consistent with design and power calculations, 819 mothers were recruited to the trial. The primary outcomes for the trial are parents’ sense of competence and self-efficacy measured using standard self-report questionnaires. Secondary outcomes include the quality of mother-infant relationships, maternal social support, role satisfaction and maternal mental health, infant social-emotional and language development, and patterns of service utilisation. Maternal and infant outcomes will be evaluated using age-appropriate questionnaires when infants are aged <2 months (pre-intervention), 9, 15, and 21 months.

**Discussion:**

We know of no previous study that has evaluated an intervention that combines the capacity of nurse and internet-based services to improve outcomes for mothers and infants. The knowledge gained from this study will inform the design and conduct of community-based postnatal mother and child support programs.

**Trial registration:**

Australian New Zealand Clinical Trials Registry ACTRN12613000204741

## Background

During their initial postnatal weeks, in many parts of Australia, Canada, the United Kingdom, and other European countries, mothers and infants are supported by community nurses in family homes and community clinics [1,2]. This includes completing maternal and infant health checks, promoting parent knowledge and attitudes relevant to child rearing, and referring infants and mothers requiring additional help to appropriate specialist services.

In the past, nurse-based community services were the principal source of professional information and support for mothers of young children. However, during the last decade the internet has transformed the provision of healthcare services. For mothers of young children, the internet now provides free, convenient, and private access to health information [3,4], the opportunity to share and exchange information [5], and interactive treatment programs designed to address problems such as depression or anxiety [6]. Evidence about the extent to which the internet is consulted by mothers of young children is available from several recent studies [7-10]. For example, a study of 360 mothers of young children attending the Emergency Department at the Royal Children's Hospital in Melbourne found that 81% of mothers had access to the internet either at home or work and 43% had sought information from the internet about their children's health [3]. Wainstein and colleagues [7] reported that 83% of mothers attending a children's hospital responded that the internet had influenced the questions that they asked their doctor, and 18% reported that information obtained on the internet led to changes in their management of their children. As well, in our recent study of nurse home-visiting in South Australia (SA), preliminary analyses identified that in this population of mothers experiencing high levels of social adversity, 80% have access to the internet either at home, through a public library or via telephone [11].

The internet has the potential to reduce barriers to accessing services, including limited availability of skilled professionals, geographic isolation, the cost and inconvenience of travel and child care, and limited flexibility in work schedules [12]. The steadily increasing penetration of home computer and internet usage with vulnerable populations now renders delivery of intervention services via the internet a potentially valuable way to address the service needs of a high proportion of mothers and infants [12]. Potential cost reductions associated with transferring in-home programs to combined nurse-internet programs include reducing the need for service providers to physically travel to distant areas on a regular basis, avoiding costs of “no-show” visits, and allowing one professional to work with multiple families during a single day.

The frequency with which mothers seek online health information has encouraged the development of a large number of new websites and “phone apps”. However, an ongoing concern for professionals and mothers is the variable quality of information provided by these online sources of information [3,4,13,14]. For example, Plantin and Daneback [14] have reported that health-related information on the internet can be misleading and occasionally, “utterly wrong” [14-16]. There is also an almost total absence of evaluations assessing the ability of websites and “phone apps” to improve maternal and child outcomes [17]. We are not aware of any previous study that has evaluated the effectiveness of a nurse-moderated group-based internet support program employed to enhance post-natal outcomes for mothers and infants. The present study was designed to address these omissions.

### Objectives

The aim of the present study is to compare the effectiveness of a single clinic-based appointment plus a nurse-led group-based internet intervention when infants were aged 0–6 months versus a single clinic/home-visit plus standard services as requested by mothers (the latter was available to mothers in both study groups). Currently, the recruitment stage of this trial was completed in December 2013; intervention delivery and follow up assessments are ongoing.

Combining a clinic-based face-to-face mother/infant assessment with a 6-month nurse-moderated, group-based internet support program has several important benefits for the provision of services to mothers and infants. First, an internet-based program does not require the expensive provision of home visits by nurses. Second, it facilitates access to support for time-poor new mothers. Third, it provides nurses with online tracking of the extent to which mothers engage with different components of an intervention such as their participation in group discussions and utilisation of information available on a website. This allows nurses to more accurately target services to individual mothers and infants. Finally, it provides mothers with credible and readily accessible information about parenting and infant development.

## Methods/Design

### Study design

The evaluation is utilising a pragmatic preference randomised trial to compare the equivalence of outcomes for mothers and infants across the two study groups. We are examining the equivalence or “non-inferiority” [18] of the intervention with standard service because: (i) there is no evidence for the effectiveness of the current home-visit plus access to subsequent standard services, and (ii) while we believe the enhanced intervention has the potential for greater benefits to mothers and infants, given a local policy commitment to some form of post-natal nurse-based health checks, the key initial question for service providers is, “Is there a potentially more cost effective method of delivering a universal contact service for all mothers and infants in South Australia?” This implies that any new approach must produce outcomes that are equivalent or not inferior to current standard services. While the study is powered for equivalence, once we have established non-inferiority, we also have the ability to examine whether the enhanced nurse-internet intervention is superior on maternal and child health outcomes.

Outcomes will be assessed 4 times from the time infants are aged <2 months (pre-intervention assessment) through to 21 months. Outcomes will include parenting competence and self-efficacy (primary outcomes), maternal-infant attachment, maternal social support, role satisfaction and mental health, infant social and emotional development, and patterns of service use by mothers and infants (secondary outcomes).

The need for randomized controlled trials that are embedded in service practice and examine questions relevant to service clients, workforces, and delivery systems has been widely recognized in the medical and public health literature [19,20]. In contrast to explanatory trials which operate under ideal conditions, pragmatic trials occur within the context of current service delivery and population needs, and ask “Does this intervention work under usual conditions?” [19]

We are using a preference-based design [21] in which service preferences are elicited from mothers at the time that they are recruited to the study. Mothers who express a “strong preference” for the intervention or for standard care are allocated to their preferred group. Mothers without strong preferences are randomized to intervention or standard care (Figure 1). The advantage of this approach is that many people refuse randomization, and/or drop out post randomization (if they don’t get their preferred service). As such, results can only be generalized to those who participate in randomization and complete the study (as low as 35% in some studies [21]). We have included those with a strong preference in this study as an “observational” cohort so we can compare outcomes in those randomized, with those who chose randomization or standard care, and thus improve generalizability of the findings to the whole population for whom the service is intended. If outcomes are similar in the randomized and preference groups then we can more clearly make inferences about the effects in the whole population.

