### Sample size

Our primary outcomes focus on mothers’ sense of competence and self-efficacy in areas relevant to parenting and problem solving with infants. These outcomes were chosen in consultation with CaFHS nurses who identified one of their primary goals as helping ensure parents feel more competent to manage challenges associated with the care of infants.

Given that the primary question for the trial focuses on testing the equivalence of the nurse-moderated group-based internet program versus standard care, we estimated that with a sample size of 200 per randomized group, we would have 80% power at alpha = 0.05 to detect a 0.25 standard deviation difference (inferiority range) between the home-visit and nurse led internet groups in the primary outcome. Thus we would have 80% power to test the hypothesis that the internet-based intervention is no more than 0.25 of a standard deviation inferior when compared to standard care on the primary outcome measures. These estimates were based on data from our current 2 year follow-up of the Nurse Home Visiting program [11]. Based on this earlier study we allowed for an attrition of 20% over 2 years in the present study. To take this into account, we aimed to recruit 240 mothers to be randomised to each study group. Figure 1 shows the participant flows in the study leading to the final trial sample.

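### The plan says the study is powered for equivalence, but 200 per group gives 80% power only for one-sided 5% non-inferiority

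*Protocol article*

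**What the plan says.** The title calls the trial "An equivalence evaluation of a nurse-moderated group-based internet support program for new mothers versus standard care", and the abstract states its aim and methods in the same terms. Under Study design the article says "While the study is powered for equivalence, once we have established non-inferiority", and then mentions the possibility of examining superiority. Under Sample size it says that "the primary question for the trial focuses on testing the equivalence of the nurse-moderated group-based internet program versus standard care".

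The power statement follows in the same paragraph. It gives 80% power "with a sample size of 200 per randomized group", with alpha 0.05, not described as one- or two-sided, and a difference of 0.25 SD labelled as the range for inferiority. It then restates the calculation as a hypothesis: "we would have 80% power to test the hypothesis that the internet-based intervention is no more than 0.25 of a standard deviation inferior". No upper bound for equivalence and no two-sided equivalence procedure appear in the article.

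**The concern.** Equivalence and non-inferiority are different claims. Equivalence requires the difference to be shown to lie above a lower bound and below an upper one; non-inferiority requires only the lower. For the same margin, alpha per test and sample size, equivalence has less power, because both tests must succeed. A study sized on the lower bound alone therefore does not have its stated power for equivalence.

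The article ties the trial to a decision about a universal postnatal service, so the form of the conclusion matters. If equivalence were tested properly at a margin like the one stated, the trial would fail to show it more often than 80% power implies, even with identical services. If only the lower bound were tested, the word equivalence would claim more than the test supports. The unqualified alpha adds a second ambiguity: a reader who takes 0.05 as two-sided, and so judges non-inferiority by a two-sided 95% interval, does not get 80% power either.

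**Working it through.** **Inputs from the Sample size section:** n = 200 per randomised group; margin 0.25 SD; alpha 0.05, sidedness not stated; power 80%.

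**Assumptions added here:** true difference zero; unadjusted comparison of two means; no clustering; 200 analysed per group; and, for equivalence only, an upper bound mirroring the stated lower one (±0.25 SD).

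**Standard error.** In SD units, SE = √(2/200) = 0.10, so margin/SE = 0.25/0.10 = 2.5.

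**Reproducing the plan's figure: non-inferiority, one-sided 5%.**
- Power = Φ(2.5 − 1.645) = Φ(0.855) = 80.4%.
- Required n = 2(1.645 + 0.842)²/0.25² ≈ 198 per group.
- Both agree with the stated 80% and 200.

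**Non-inferiority, one-sided 2.5% (two-sided 95% interval).**
- Power = Φ(2.5 − 1.960) = Φ(0.540) = 70.5%.
- Required n = 2(1.960 + 0.842)²/0.25² ≈ 251.2, so 252 per group.
- This does not reproduce the plan.

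**Equivalence by two one-sided tests (TOST) at ±0.25 SD.** Power = 2Φ(margin/SE − z) − 1.
- 5% per side: 2 × 0.804 − 1 ≈ 61% (60.5% by numerical integration with the t distribution). For 80% power, n = 2(1.645 + 1.282)²/0.25² ≈ 274 to 275 per group.
- 2.5% per side: 2 × 0.705 − 1 ≈ 41%. For 80% power, about 337 per group.

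| Test, 200 per group | Power | n per group for 80% |
|---|---|---|
| Non-inferiority, one-sided 5% | 80.4% | 198 |
| Non-inferiority, one-sided 2.5% | 70.5% | 252 |
| Equivalence, 5% per side (assumed ±0.25 SD) | about 61% | 275 |
| Equivalence, 2.5% per side (assumed ±0.25 SD) | about 41% | 337 |

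Of these four readings, only the first matches the article's figures.

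**Sensitivity of the 61% to the added assumptions (illustrative values, not from the article).**
- Baseline adjustment with correlation 0.5 multiplies the variance by 0.75. SE = 0.0866, margin/SE = 2.887, and equivalence power = 2Φ(1.242) − 1 ≈ 79%.
- A design effect of 1.1 gives SE = 0.1049, margin/SE = 2.384, and equivalence power = 2Φ(0.739) − 1 ≈ 54%.
- A non-zero true difference lowers equivalence power further.

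**The case against.** The strongest reply is that the article uses the two terms as near-synonyms. Study design introduces equivalence and non-inferiority together as one idea, asks for outcomes that are equivalent or no worse, and plans non-inferiority followed by superiority, which is a non-inferiority framework. Sample size states the operative hypothesis in one direction. A careful reader can tell which test was sized, and the service question of whether a potentially cheaper model is no worse needs only the lower bound. All of this stands, and it makes the correction easy. It does not make the claim of power for equivalence true, nor does it allow an equivalence conclusion from a one-sided test.

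A second reply is that the 61% belongs to a test that the article never specifies. That is right: the symmetric ±0.25 SD bound is an assumption, as are the unadjusted analysis and the absence of clustering, while the Analysis plan mentions longitudinal models and clustering by nurse. The figure is conditional. Without an upper bound, however, no equivalence power can be stated at all.

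Stronger readings are tempting but unsupported:
- A reader might infer that the sample size is miscalculated. It is not; 200 reproduces for one-sided non-inferiority.
- A reader might infer that the superiority step is underpowered. The article claims only to be able to examine superiority and states no power for it.
- A reader might infer that the final report will claim equivalence from the lower bound alone. The article does not say so; this is a risk that the wording leaves open.
- The attrition allowance is a separate matter and is not needed for this point.

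**Conclusion.** The concern holds as a fault of labelling and of unstated sidedness, not of arithmetic. The claimed 80% power belongs to non-inferiority at one-sided alpha 0.05 with a true difference of zero (80.4%). It falls to 70.5% if alpha 0.05 is read as two-sided. For equivalence the article gives no upper bound; under an assumed ±0.25 SD margin with an unadjusted, unclustered comparison of 200 per group, power is about 61% at 5% per side and about 41% at 2.5% per side. Since the sized hypothesis can be recovered from the text and the sample size stands, this is a needed correction of wording rather than a defect that undermines the design.

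**What to change.** - Call the trial non-inferiority in the title, the abstract and its aim, Study design and Sample size, and delete the statement that it is powered for equivalence.
- State that alpha 0.05 is one-sided. Give the decision rule: with outcomes scored so that higher is better, non-inferiority is concluded if the one-sided 95% lower confidence bound for internet program minus standard care lies above −0.25 SD.
- State that equivalence will not be concluded from this one-sided test.
- If equivalence is still to be claimed, give both bounds and the alpha per side, and report the lower power (about 61% at ±0.25 SD with 5% per side, under the assumptions above). The margin should not be widened merely to recover 80% at the existing sample size.

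The cost is wording only. The 200 per group, the 0.25 SD margin and the hypothesis that was sized are unchanged, and no further mothers are needed on this account. Recruitment is complete but follow-up is still under way, so the correction can be made before the final analysis. The price is a less favourable power figure for any equivalence claim.

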### Procedure

Staff in birthing hospitals in South Australia ask all new mothers for their consent to be contacted by CaFHS to arrange a health check during their initial postnatal weeks. Approximately 93% of mothers give consent and are subsequently contacted by CaFHS administrative officers who arrange appointments for mothers with nurses either in family homes or at CaFHS clinics. For the purpose of the present study, mothers were advised by hospital staff about the study and the possibility that they may be asked to take part in it.

When subsequently contacted by CaFHS administrative officers, mothers were reminded about the study and verbal consent for their participation was sought. The script used by administration officers to inform mothers of the trial is included in Additional file 1. Mothers who consented were asked if they had a strong preference to participate in the internet-based group or receive standard care. As described above, those who expressed a strong preference for a particular arm of the study were enrolled in their preferred group. Those who did not have a strong preference were randomised to the intervention or standard care groups [23].

The contact details of mothers who gave verbal consent to participate in the study were provided to the research team, who contacted mothers by telephone and explained the study in more detail. Following the telephone call, mothers who confirmed their verbal consent were visited by a research assistant who completed a written consent process and arranged for completion of the 2-month (pre-intervention) assessment. At the time of their pre-intervention assessment, mothers were provided with a username and password for the internet-based intervention and given initial training in the use of the program. When they logged onto the program, mothers were welcomed to their group by the nurse group leader and proceeded with the intervention over the following six months.

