### Intervention and comparison condition

#### Standard care

As noted, in South Australia all families of newborns are offered a clinic or home-visit by a Child and Family Health community nurse during the initial postnatal weeks. The aim of the home-visit is to: (i) complete maternal and child health checks, (ii) provide comprehensive, information-based support to families of new infants, (iii) offer guidance and information about future child development, and (iv) link families to other services where this is required [24]. As this service is offered to all families of newborns in South Australia, it is relatively expensive involving more than 18,000 visits to homes across the State annually with each visit lasting about 60–90 mins. Although clinic visits are an option (or a visit in a ‘safe place’ for women who are considered not safe enough to visit at home) most parents prefer a home visit. Following this visit, mothers are encouraged to bring children for health checks at community clinics when the children are aged 6 and 18 months. A range of other services are also available at over 120 clinic sites across South Australia, with additional support including a telephone helpline, day-long support at community clinics for parents who need additional support with problems such as feeding or settling; and residential care for families with major unresolved problems with infant feeding, settling, and sleeping problems.

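### Similar outcomes in the randomised and preference groups cannot extend the result to mothers who strongly prefer standard care, because none of them is allocated to the internet service

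*Protocol article*

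**What the plan says.** All of this is in the protocol article.

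- **Question (Study design).** The key question for service providers is put as "Is there a potentially more cost effective method of delivering a universal contact service for all mothers and infants in South Australia". The article adds: "This implies that any new approach must produce outcomes that are equivalent or not inferior to current standard services".
- **Allocation (Study design and Procedure).** Only mothers without a strong preference are randomised. Mothers with a strong preference "for the intervention or for standard care are allocated to their preferred group". The Procedure section confirms it: "those who expressed a strong preference for a particular arm of the study were enrolled in their preferred group".
- **Use of the preference groups (Study design).** They are kept as an observational cohort, to "thus improve generalizability of the findings to the whole population for whom the service is intended". The stated rule is that if outcomes are similar in the randomised and preference groups, "we can more clearly make inferences about the effects in the whole population".
- **Analysis plan.** All mothers are pooled in one model. Dummy variables mark randomised versus preference-based participation in the internet program, with possible interactions with time and baseline psychosocial adversity.
- **Sample size.** 200 per randomised group, 80% power, alpha 0.05, margin 0.25 SD. The calculation covers the randomised groups only.
- **Discussion.** The policy aim is narrower here: the service might suit many mothers, with home visits directed to those needing more intensive support.

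**The concern.** The question concerns a service for everyone, while the only unbiased comparison of the two services is made in mothers content to receive either. The protocol proposes to bridge the gap by checking whether preference mothers resemble randomised mothers. That check compares levels of outcome. The non-inferiority question is about an effect, the difference between two services in the same kind of mother. For mothers who strongly prefer standard care, one side of that difference is never observed.

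At stake is what a positive result may be taken to mean. If non-inferiority is shown in the randomised mothers and the preference groups look similar, the rule as written licenses a statement about the whole population. The data would support that statement only under an assumption that the article does not name and the trial cannot test.

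**Working it through.** **Step 1. The plan's own figure.** With true difference 0, margin 0.25 SD, one-sided 5% and 80% power, n per group = 2 × (1.645 + 0.842)² / 0.25² ≈ 198, which reproduces the stated 200. The article does not state the sidedness of alpha; one-sided 5% is the reading that fits (one-sided 2.5% would need 252). At 200 per group the standard error is √(2/200) = 0.10 SD. The probability of showing non-inferiority when the true effect in randomised mothers is e is Φ((0.25 + e)/0.10 − 1.645): 80% at e = 0 and 44% at e = −0.10. These figures describe mothers without a strong preference only.

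**Step 2. What the allocation rule lets the trial see.**

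| Mothers | Seen on internet service | Seen on standard care |
|---|---|---|
| No strong preference | yes, randomised | yes, randomised |
| Strongly prefer internet service | yes, by choice | no |
| Strongly prefer standard care | **no** | yes, by choice |

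The effect in the third row needs both cells. One is empty by design, so a larger sample does not help.

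**Step 3. What the similarity check can detect.** Suppose mothers who strongly prefer standard care have the same mean on standard care as mothers randomised to it. The comparison then shows no difference, and it shows none whether their effect on the internet service would be 0, −0.25 or −1 SD, because that quantity enters no observed mean. The dummy variables in the Analysis plan mark preference-based participation in the internet program, and those mothers are the ones who wanted it. An interaction with baseline adversity could carry the randomised effect over to mothers with a different adversity profile, but only by assuming that preference itself does not alter the effect.

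**Step 4. How much the empty cell could matter.** Let s be the share strongly preferring standard care, −d their unobserved effect in SD, and e the effect in everyone else. The population average is −s·d + (1 − s)·e. Setting it to −0.25 gives d = (0.25 + (1 − s)·e)/s.

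| Assumed s | d if e = 0 | d if e = −0.10 |
|---|---|---|
| 0.1 | 2.5 | 1.60 |
| 0.2 | 1.25 | 0.85 |
| 0.3 | 0.83 | 0.60 |
| 0.4 | 0.625 | 0.475 |

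For example, at s = 0.3 and e = −0.10: (0.25 − 0.07)/0.3 = 0.60.

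**Step 5. Plausible range of s.** The split of the 819 recruits is in Figure 1, which is not shown. If exactly the target of 2 × 240 = 480 was randomised (an assumption), preference mothers of both kinds number 819 − 480 = 339, or 41%, and s among recruits lies between 0 and 41%.

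**The case against.** The best defence is that the protocol knows its limits. It says that results from a trial of this kind generalise only to those who accept randomisation and complete the study, it labels the preference mothers observational, it words the inference conditionally, and it ties power to the randomised groups. It makes no explicit non-inferiority claim for the preference mothers. A conventional trial would probably lose many of them altogether, so the design gains information. All of this stands, and it makes the point one of wording and inference rather than a design fault. It does not rescue the rule itself: a hedged inference from similar levels to a common effect still needs the missing assumption.

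A condensed article may also leave a sensitivity analysis to the full plan. That is fair. The finding rests on the inference rule that the article states, not on the absence of a tipping-point analysis.

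Three stronger readings are tempting, and the document does not support them:

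- *Mothers who strongly prefer standard care would be the ones harmed.* Nothing in the article shows this. It says there is no evidence that the current home visit with later standard services is effective. Their effect is unobserved, not known to be worse.
- *The group must be large, because* "most parents prefer a home visit". That remark compares home with clinic visits within standard care. It does not concern a strong preference against the internet program at recruitment.
- *The trial sets out to replace the visit for all mothers.* The article asks about a more cost-effective universal contact. The intervention keeps one clinic appointment, standard services stay open to both groups, and the Discussion speaks of many mothers rather than all.

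**Conclusion.** The point holds as a limit on what may be concluded. The all-mothers question and the allocation rule are both explicit, and together they leave the effect in mothers who strongly prefer standard care unidentified. The rule offered to bridge the gap is not valid for them without assuming that the effect does not depend on preference.

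A reader might go on to infer that the randomised comparison is biased. It is not on this account: it remains valid for mothers without a strong preference, and the issue is generalisability.

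The size is open. At a 10% share and zero effect elsewhere, the unobserved deficit would have to be 2.5 SD, ten times the margin, and the concern would be of little practical weight. At 40% it would be 0.625 SD, or 0.475 SD if the effect elsewhere were −0.10 SD. These figures rest on assumed shares and on one common effect in all other mothers, including those who chose the internet service, whose own effect is also not directly observed. They show what is possible, not what is likely.

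**What to change.** 1. In Study design, state that the non-inferiority conclusion applies to mothers without a strong preference.
2. In the same section, rewrite the rule on similar outcomes. Either limit wider statements to a service in which strong preferences are honoured, which agrees with the Discussion, or state openly that extension to all mothers assumes an effect that does not depend on preference and that these data cannot test.
3. Before any statement about all mothers, report the tipping point: from the recorded share s and the estimated effect in other mothers, the deficit d that would bring the population-weighted effect to −0.25 SD. Add that s is measured among recruits (819 of the 1825 eligible mothers contacted, 45%) and may differ in the wider population.

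The cost is a narrower claim, a few sentences and one calculation from counts already recorded. No new data, recruitment or change to the randomised analysis is needed, and follow-up was still under way when the article was written.
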